**Power calculation and sample size:** No previous RCT examined effects of MT on the PBQ; two small RCTs included in our systematic review [25] and a recent non-randomized study [29] examined mother-infant bonding, but provided insufficient data for meta-analysis. Studies using the PBQ with other interventions found effects ranging from around 0.25 ([44], posttest) through 0.5 ([45], mothers at 1/6 months), 1.4 ([46], 4 months), 2 ([45], fathers at 1/6 months), 9 ([44], 3 months), with SDs ranging from 4 to 12. Assuming a difference of 4 points on the PBQ ( $SD = 8$ ) as a minimal clinically important difference for this study, power of 80% will be achieved for each main effect (each tested on a two-sided 2.5% significance level, i.e. 5% with Bonferroni correction for two tests) with a sample size of 155. Taking into account some clustering by country (ICC 0.01; 5 countries), this is increased to 203. To allow for 20% attrition, we will aim to include 250 infants (50 in each country) and their parents. This sample size will also ensure power for testing proportion differences of about 15% (e.g. binary analysis of problematic bonding; re-hospitalization). Special considerations are needed for multiple pregnancies (twins, triplets, etc.), which account for about 2% in Hordaland [4], but are more common in NICUs due to their elevated risk of preterm birth. Including all siblings would serve to increase the sample size, but may lower the resulting power due to cluster effects.

Therefore, we will only formally enroll and analyze the first-born sibling of each multiple pregnancy, although all will receive the intervention.

**Data analyses:** All randomized participants will be included in the main analysis (intention-to-treat). Descriptive statistics will characterize basic properties of the sample and provide information for power calculation for the multi-center study. Effects will be examined by testing the randomized groups for differences in the primary endpoint (t-test or Mann-Whitney; change in PBQ scores to 6 months CA), as well as by fitting linear mixed models. In the first modeling step we will assess the effect of the first randomization (Fig. 1) using the following model:

$$PBQ_{it} = \beta_0 + \beta_1 time_t + \beta_2 gr_i + \beta_{12} time_t gr_i + U_i + \varepsilon_{it} ,$$

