where  $PBQ_{it}$  denotes the PBQ score for participant  $i$  at measurement  $t$ ,  $time_t$  the time from baseline at measurement  $t$  and  $gr_i$  the randomization group of participant  $i$ .  $\beta_0$ ,  $\beta_1$ ,  $\beta_2$  and  $\beta_{12}$  are the coefficients estimated in the model,  $U_i$  is an individual random term per participant and  $\varepsilon_{it}$  an independent, identically distributed error term. In the second step we refine the model to take into account both randomization steps, leading to the extended model:

$$PBQ_{it} = \beta_0 + \beta_1 time_t + \beta_2 grR1_i + \beta_{12} time_t grR1_i + \beta_3 grR2_i + \beta_{13} time_t grR2_i + U + \varepsilon_{it} ,$$

with the same notation as above and  $grR1_i$  and  $grR2_i$  denoting the groups from the first and second randomization, respectively. In these models  $\beta_1$  describes a group-independent time effect,  $\beta_2$  and  $\beta_3$  a time-independent group effect, and  $\beta_{12}$  and  $\beta_{13}$  the time-dependent change of the group effect. We will investigate both linear and simple contrasts (comparing each time point with the baseline) in time to assess the treatment effect. The same analyses will be done for the secondary outcomes; using an analogous generalized linear mixed model for binary outcomes. Per-protocol analyses will include those who received at least 6 MT sessions in the NICU and at least 5 MT sessions post-discharge, respectively; these are considered the minimum numbers for the intervention to be successful. Additionally, we will conduct exploratory statistical analyses for prespecified subgroups (sex; GA at birth [ $<28$  wks, 28 to  $<32$  wks, 32 to  $<35$  wks]; hearing status at discharge [normal vs. abnormal]; bonding at baseline [PBQ impaired bonding score  $\geq 11$  vs.  $<11$ ]) as well as qualitative/mixed-methods analyses of process data to maximize learning.

**Data management plan:** To promote transparency and applicability of trial results and to facilitate re-analysis by other researchers while also protecting anonymity, de-identified individual patient data will be made available through the Norwegian Centre for Research Data (NSD).

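### The primary test uses unadjusted change in PBQ while the power paragraph leaves its SD of 8 and the baseline correlation undefined; adjusting for baseline PBQ would be at least as efficient at no cost

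*Combined protocol and SAP*

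**What the plan says.** All references are to section 2.2.4 of the combined protocol and SAP unless stated otherwise.

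- **Primary comparison (Data analyses).** Effects are examined by "testing the randomized groups for differences in the primary endpoint (t-test or Mann-Whitney; change in PBQ scores to 6 months CA"), and also by linear mixed models. The text does not say which of the two is decisive.
- **Mixed models (Data analyses).** Baseline is one of the repeated outcomes. Each model has a time-independent group term and a time-by-group term for the first randomization; the extended model adds the same pair for the second. Treatment effects are assessed by linear contrasts in time and by "simple contrasts (comparing each time point with the baseline"). Baseline PBQ is not a covariate in any model.
- **Power (Power calculation and sample size).** The basis is "Assuming a difference of 4 points on the PBQ ( $SD = 8$ ) as a minimal clinically important difference for this study". The published studies listed just before are summarised "with SDs ranging from 4 to 12". The claim is that "power of 80% will be achieved for each main effect". Significance is judged two-sided at 2.5% per main effect, a Bonferroni split of 5% over the two tests, and the total before any inflation is 155. The clustering step reads: "Taking into account some clustering by country (ICC 0.01; 5 countries), this is increased to 203". After an allowance for 20% attrition the target is 250 infants.
- **Timing of baseline (Randomization, allocation concealment and blinding).** Baseline assessment comes before the first randomization, and so before the second as well.
- **Primary time point (section 2.2.3).** 6 months corrected age.

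**The concern.** The quantity analysed is a difference between two PBQ measurements. Its SD depends on the SDs at the two times and on r. It equals the SD of a single score only in a special case. The power paragraph gives one SD, does not name the variable it belongs to, and gives no r. The claim of 80% power per main effect is therefore not tied to the test that will be run.

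The choice of test has a cost of its own. Subtracting baseline fixes its coefficient at 1; regression on baseline estimates that coefficient from the data. In large samples the regression is never less precise, and when r is moderate or low the gain is considerable. The covariate is already collected before randomization, so the plan gives up precision on its primary endpoint for nothing in return.

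**Working it through.** **Inputs.** From the plan: difference 4, SD 8, two-sided alpha 0.025, N = 155 in total (77.5 per level of each factor), 203 after clustering, 250 enrolled. The correlation r is not in the documents. It is an assumption here and is shown over a range.

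**1. Reproduce the plan's figure.** A two-sample t-test (noncentral t) with standardised difference 4/8 = 0.5 needs 77.3 per group, 154.6 in total, for 80% power. At N = 155 power is 80.1%. The stated 155 is therefore right if 8 is the SD of the variable tested. The clustering step is also roughly recovered: 155 x (1 + (31 - 1) x 0.01) = 201.5, against the stated 203.

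**2. Variances of the two analyses.** Let s0 and s1 be the SDs at baseline and at 6 months.
- Change: s0² + s1² - 2·r·s0·s1
- Baseline-adjusted: s1²·(1 - r²)
- Change minus adjusted: (s0 - r·s1)², which is never negative.

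Adjustment is thus at least as efficient whatever the SDs; the one degree of freedom it uses is negligible here. With s0 = s1 = s, the variances are 2(1 - r)s² and (1 - r²)s², with ratio 2/(1 + r): 1.54 at r = 0.3 and 1.33 at r = 0.5.

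**3. If 8 is the SD of scores, equal at both times.** SD of change = 8·√(2(1 - r)); adjusted SD = 8·√(1 - r²).

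| r | SD of change | Adjusted SD | Change power, N = 155 | Adjusted power, N = 155 | Change power, N = 200 | Adjusted power, N = 200 |
|---|---|---|---|---|---|---|
| 0.2 | 10.12 | 7.84 | 57.9% | 81.8% | 70.4% | 91.1% |
| 0.3 | 9.47 | 7.63 | 64.3% | 84.0% | 76.7% | 92.5% |
| 0.4 | 8.76 | 7.33 | 71.8% | 87.0% | 83.3% | 94.4% |
| 0.5 | 8.00 | 6.93 | 80.1% | 90.7% | 89.8% | 96.5% |
| 0.6 | 7.16 | 6.40 | 88.7% | 94.7% | 95.4% | 98.4% |

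N = 155 is the plan's own effective size once its clustering allowance is used up. N = 200 is 250 x 0.8, counted in full as if clustering cost nothing. At N = 200 the change test has 79.9% power at r = 0.35, so break-even lies between about 0.35 and 0.5, depending on how much of the allowance is consumed.

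**4. Unequal SDs.** At N = 155 with a 6-month SD of 8, the SD of change equals 8 when r = s0/(2·s1). Break-even is 0.375 if baseline SD is 0.75 times the 6-month SD, and 0.625 if it is 1.25 times.

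**5. If 8 is the SD of change.** The planned test has its 80.1% at N = 155, with no shortfall. With equal SDs the adjusted variance is (1 + r)/2 times the change variance: 0.65 at r = 0.3, 0.70 at 0.4 and 0.75 at 0.5. Adjustment would still gain precision.

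**6. The mixed model.** The group terms leave the arms free to differ at baseline. With complete data, the between-arm difference in a simple contrast of 6 months against baseline is then the difference in mean change, the same quantity as the t-test with the same variance.

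**The case against.** - **The SD.** The text does not say that 8 is the SD of scores. That is the natural reading, since the cited effects are labelled by assessment time and the power paragraph does not mention change, but it is still an inference. A reader might conclude that the trial is underpowered. The documents do not support that: what they show is an undefined SD and an unstated correlation. This objection stands in full.
- **The threshold.** A reader might also infer that 80% power requires r of at least 0.5. That holds only with equal SDs and an effective N of 155. Randomization is individual, so it is arguable how much of the country allowance is really lost.
- **The size of r.** It is tempting to say that r must be low because one measurement is taken in the NICU and the other at 6 months corrected age. The plan gives no correlation, so a low r is possible but not shown.
- **The mixed model.** The plan also includes linear contrasts over all time points, which use more data than a two-point change, and it does not name the t-test as decisive. This is fair, but the simple contrast that targets the primary time point is still a change contrast, and nothing planned uses baseline as a covariate.
- **Validity.** Comparing change between randomized arms is unbiased and keeps the type I error rate. This stands, and it limits the severity of the point.

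**Conclusion.** The point holds as an efficiency and definition issue that should be fixed. The primary endpoint is analysed as unadjusted change, and the 80% power claim cannot be matched to that analysis without knowing which SD the 8 is and what r was assumed.

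On the reading that 8 is the SD of scores, equal at both times, the change test falls below 80% when r is under about 0.5 (effective N of 155) or under about 0.35 (200 analysed, no clustering loss). On the other reading nothing is lost against the stated power. On either reading, adjusting for baseline is at least as precise. With score SD 8 and N = 155 it lifts power by about 20 percentage points at r = 0.3 and about 11 at r = 0.5.

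The algebra in favour of adjustment is certain; the size of the gain depends on r, which is unknown.

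**What to change.** 1. Make the primary analysis a linear regression of 6-month PBQ on both randomized factors, with the PBQ taken before the first randomization as covariate. Alternatively, use a mixed model that constrains the baseline mean to be common across the arms of both randomizations. Constraining only the first would leave the change-contrast loss in place for the second powered main effect.
2. Name this one analysis as decisive for the primary endpoint.
3. Do the same for EPDS and PSS where a baseline measurement exists.
4. In the power paragraph, state whether 8 is the SD of scores or of change, give the assumed r (or a range), and restate the power for the chosen analysis.

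The cost is a change of wording in the analysis and power paragraphs, made before unblinded outcome data are seen. No new data, visits or participants are needed.

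### Section 2.2.4 does not say which analysis decides the primary question, and the change-score comparison it lists uses baseline PBQ less efficiently than baseline adjustment would

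*Combined protocol and SAP*

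**What the plan says.** All of the relevant text is in section 2.2.4, apart from the time points in section 2.2.3.

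- **Endpoint.** Section 2.2.3 fixes the outcome (PBQ) and the primary time point (6 months CA). PBQ is also measured at baseline, shortly before discharge, and at 12 months CA.
- **Analysis.** Group differences are to be examined by "t-test or Mann-Whitney; change in PBQ scores to 6 months CA), as well as by fitting linear mixed models". The first model contains the first randomization only; the second contains both. Each has time, group and time-by-group terms and a random term per participant. Linear and simple contrasts in time are both planned, and neither is named as primary.
- **Population.** "All randomized participants will be included in the main analysis (intention-to-treat".
- **Power.** "Assuming a difference of 4 points on the PBQ" and an SD of 8, the plan states that "power of 80% will be achieved for each main effect" "with a sample size of 155", "each tested on a two-sided 2.5% significance level, i.e. 5% with Bonferroni correction for two tests". The total is raised to 203 for clustering by country and to 250 for 20% attrition. The text does not say whether 8 is the SD of a score or of a change, and gives no correlation between visits.

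**The concern.** A plan that allots 2.5% to each main effect needs one test per main effect to spend it on. Here several are listed without ranking, so the deciding result could be picked once the data are known, and the Bonferroni split does not cover that choice.

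The change score is also an inefficient use of baseline. When the baseline-to-6-month correlation is low, subtracting baseline adds more noise than it removes. Baseline here is taken in the NICU and the endpoint at 6 months CA, so a modest correlation is possible, though the documents give no figure.

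Two parts of the plan also do not fit together. The sample size is inflated for country, but no listed test or model has a country term. A change-score test cannot include participants who lack a 6-month PBQ, although the main analysis is said to include everyone randomized.

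**Working it through.** **Inputs (section 2.2.4).** Difference 4; SD 8; two-sided level 0.025 per factor; 80% power; 155 before inflation; 203 after clustering (ICC 0.01, 5 countries); 20% attrition; 250 enrolled. The correlation r is not in the documents, so a range is shown. SDs are assumed equal at baseline and 6 months.

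**Step 1: reproduce the plan's figure.** Total N = 4 × (2.241 + 0.842)² × 8²/4² = 152 by the normal approximation. The noncentral t gives 154.6, hence 155. With 156 (78 per arm) in 5 countries of 31.2, the design effect is 1 + 30.2 × 0.01 = 1.302, and 156 × 1.302 = 203. Then 203/0.8 = 254, close to the stated 250. So 155 is the size for a plain two-group comparison of a variable with SD 8.

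**Step 2: variance of the two approaches.**

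- Change score: 2 × SD² × (1 − r).
- Baseline-adjusted 6-month score: SD² × (1 − r²).
- Ratio, adjusted to change: (1 + r)/2, which is 0.65 at r = 0.3 and 0.75 at r = 0.5.

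The ratio does not depend on which SD the 8 refers to. The mixed-model 6-month simple contrast does not recover the loss. Baseline enters as an outcome with its own group coefficient, so with complete data the contrast is again a difference in mean change.

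**Step 3: power if 8 is the score SD.** The SD of change is then 8 × √(2(1 − r)), and the adjusted residual SD is 8 × √(1 − r²). Power is from the noncentral t at level 0.025. The 200 completers are 250 × 0.8.

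| r | SD of change | Change, N = 155 | Adjusted, N = 155 | Change, N = 200 | Adjusted, N = 200 |
|---|---|---|---|---|---|
| 0.2 | 10.12 | 58% | 82% | 70% | 91% |
| 0.3 | 9.47 | 64% | 84% | 77% | 93% |
| 0.4 | 8.76 | 72% | 87% | 83% | 94% |
| 0.5 | 8.00 | 80% | 91% | 90% | 97% |
| 0.7 | 6.20 | 96% | 98% | 99% | >99% |

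Break-even at 80% is r = 0.5 for N = 155 and about 0.35 for 200 completers with no design effect. If the clustering is as large as the plan assumes, 200 completers are worth about 200/1.302 = 154, so the N = 155 columns apply.

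**Step 4: power if 8 is the SD of change.** The change-score test then has the stated 80% at N = 155 whatever r is, and the adjusted analysis still has (1 + r)/2 of its variance.

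**Step 5: error rate from choosing among routes.** Null simulation for one factor: 20,000 runs at each of r = 0.3, 0.5 and 0.7; 100 per group; complete normal data; equal correlation between visits; visits assumed at 0, 2, 8 and 14 months. The table gives the chance that at least one listed p-value is below 0.025.

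| Routes counted as success | Per factor |
|---|---|
| t-test or Mann-Whitney on change | 3.0–3.1% |
| plus mixed-model 6-month contrast | 3.2% |
| plus linear trend | 5.3–5.5% |

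Treating the two factors as independent, the last two rows give 1 − (1 − 0.032)² = 6.3% and 1 − (1 − 0.054)² = 10.5%, against an intended 5%.

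**The case against.** Several stronger readings are tempting, and the documents do not support them.

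*The trial is underpowered.* This would require 8 to be a score SD and r to be low. The plan states neither. The cited studies are described only as "with SDs ranging from 4 to 12", with no indication whether these are SDs of scores or of change. Nor can the N = 155 figures be quoted as the power of a t-test that ignores country, since that test would use about 200 completers. A shortfall is possible but not shown.

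*The primary test discards the baseline.* A change score uses baseline, only less well than adjustment does. The text also does not call the change-score test primary; it sets it beside the mixed models. Each listed test is valid under randomization, so the case for adjustment is one of efficiency.

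*The false-positive rate is far above nominal.* Also counting the discharge and 12-month contrasts would take the simulated rate to about 8% per factor. But section 2.2.3 fixes 6 months CA as the primary time point, and section 2.2.4 only says that contrasts will be investigated. The t-test and Mann-Whitney are alternatives on the same quantity. For the 6-month routes alone the excess is small.

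*Intention-to-treat is abandoned.* The mixed models can use participants with incomplete follow-up, and section 2.3 explains inclusion in terms of compliance. The conflict is confined to the change-score test, but it remains open while no analysis is named as the main one.

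What survives all of this is that no deciding analysis is named, that adjustment gains precision for any r below 1, and that the SD and correlation behind the power are unstated.

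**Conclusion.** The point holds in a limited form. The plan leaves the deciding analysis open among a t-test, a Mann-Whitney test and mixed-model contrasts. The cost in type I error is modest for the 6-month routes (2.5% to about 3% per factor) and roughly a doubling only if the linear trend may also count. These rates rest on the simulation's assumed visit times and complete normal data.

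The loss of efficiency follows from the variance formulas, given equal SDs: 35% of the change-score variance could be saved at r = 0.3 and 25% at r = 0.5. Whether the stated 80% power is missed is conditional. It is missed below r = 0.5 at N = 155, or below about 0.35 with 200 completers and no design effect, if 8 is the score SD. It is not missed if 8 is the SD of change. The missing country term and the exclusion of participants without a 6-month PBQ are further gaps that the same rewording closes.

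**What to change.** Rewrite the Data analyses paragraph of section 2.2.4 as follows.

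1. Name one primary analysis per factor, tested at 2.5%: the difference in mean PBQ at 6 months CA from a likelihood-based longitudinal model (or ANCOVA with multiple imputation). Include all randomized participants, adjust for baseline PBQ and country, and include both randomization factors.
2. Do not adjust the NICU factor for the discharge PBQ, which is measured after that intervention has begun. For the post-discharge factor the discharge PBQ may serve as covariate, but only if the plan states that it is completed before the second randomization. Section 2.2.3 places the assessment one to two days before discharge and section 2.2.4 places the randomization one day before, so the order is not settled as written.
3. Make the t-test, Mann-Whitney, linear-trend and other time-point results sensitivity or secondary analyses that do not decide success.
4. State whether the SD of 8 refers to scores or to change, and what correlation the 80% power assumes.

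Adjustment for GA stratum is optional. The cost is wording only: baseline PBQ, discharge PBQ and country are already collected.

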#### **2.2.4 Trial procedures, statistical considerations, and data management**

**Randomization, allocation concealment and blinding:** After informed consent and baseline assessment, participants will be randomly assigned to NICU-MT or standard care using a computer-generated randomization list, with ratio 1:1, in blocks with sizes of 2 or 4 varying randomly, using email and an online system. The random allocation sequence will be generated and administered by people with no involvement in the clinical work to ensure allocation concealment. One day before discharge to home, participants will be randomized a second time to post-discharge MT or standard care in a 1:1 ratio, using the same procedures. This two-step randomization was chosen as the best way to create balance among those remaining in the study for the aftercare phase, and to avoid differential drop-out in the NICU phase due to expectations for the aftercare phase. In multiple pregnancies, only the first-born infant will be included and randomized, while remaining siblings will receive the same interventions for ethical and practical reasons. Blinding of interventions is not possible, but all outcomes that are not self-reports will be blinded, and success of blinding will be tested.

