### 2.3 APPLICABILITY OF THE RESULTS OF LONGSTEP

The pragmatic nature of this trial and its high clinical applicability are reflected in several dimensions, as described in the pragmatic-explanatory continuum indicator summary (PRECIS) [47]. Eligibility criteria are designed to be as inclusive as possible to promote applicability of the evidence with respect to a broad population. Broad inclusion criteria ensure enrolment of participants with heterogeneous characteristics similar to those seen by clinicians in daily practice, and exclusion criteria are narrow and exist to ensure infant safety. Another pragmatic dimension of this trial is flexible MT delivered by a qualified music therapist. Instead of including infants in a narrow PMA range, we broaden the range of inclusion and instead tailor MT to infant PMA, while incorporating family and cultural preferences. Additionally, we do not restrict if or how co-interventions will be delivered. Both parallel groups will receive standard care. Analysis of primary outcome will include all individuals regardless of compliance in order to test if the intervention works under usual conditions, with all the noise inherent therein. As a limitation it should be noted that clinical benefits as well as resulting societal benefits, related to disability prevention and economic outcomes, are likely to occur over a longer-term perspective. To address this, we will also include the possibility in the consent forms to collect later follow-up data, but these will be beyond the present project. In summary, this pragmatic trial will determine the effects of MT under usual conditions, and the design as a multicenter trial will further ensure wide generalizability.

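### The primary test and both mixed models have no therapist term, so if outcomes differ between music therapists the standard errors for the MT effects will be too small; a partially nested sensitivity analysis should be prespecified

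*Combined protocol and SAP*

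**What the plan says.** All references are to the combined protocol and SAP.

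- **Analysis (section 2.2.4, Data analyses).** Change in PBQ to 6 months corrected age is compared by t-test or Mann-Whitney, and linear mixed models are fitted. In those models the term U "is an individual random term per participant and" the remaining error is independent and identically distributed. No term for therapist, site or country appears, and no cluster-robust standard error.
- **Sample size (section 2.2.4).** The target is stated as "power of 80% will be achieved for each main effect". Alpha is divided between the two factors, which are "each tested on a two-sided 2.5% significance level, i.e. 5% with Bonferroni correction for two tests". The only cluster allowance is for country: "Taking into account some clustering by country (ICC 0.01; 5 countries), this is increased to 203". The final recruitment target follows from expected losses: "To allow for 20% attrition, we will aim to include 250 infants (50 in each country) and their parents".
- **Delivery (sections 2.2.2 and 2.3).** Sessions are individual in both phases, tailored to the infant and family, and include psychosocial support of the parent. Section 2.3 describes "flexible MT delivered by a qualified music therapist" and says that the multicentre design will further ensure wide generalizability.
- **Not given.** The readable text states neither the number of therapists nor a therapist ICC. The site list to which the recruitment paragraph in section 3 refers back is not part of it.

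**The concern.** When a treatment is delivered by individual practitioners, part of each patient's outcome may depend on who delivered it. That makes outcomes within a therapist's caseload correlated. The correlation arises only among families who receive MT, so it does not cancel when MT is compared with standard care.

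The two provisions in the plan that look relevant do not deal with it:

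- The participant intercept captures correlation between repeated measurements on one family. It is independent between families and says nothing about two families who share a therapist.
- The country allowance raises the number recruited. A larger sample does not repair a standard error computed as if families were independent. Country is also present in both arms, so under individual randomization it largely cancels from the difference, and therapist does not.

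At stake are the size of the tests for the two main effects, the width of their intervals, and whether a result can be read as an effect of MT in general or only of MT as given by these particular therapists.

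**Working it through.** **1. The plan's own sample size**

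Inputs from section 2.2.4: difference 4, SD 8, two-sided alpha 0.025, power 80%, ICC 0.01 over 5 countries, 20% attrition.

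- Per arm: 2 × (2.2414 + 0.8416)² × 8² / 4² = 76.04, rounded up to 77, so 154 in total. The t-based solution is 77.31 per arm, 154.6 in total, matching 155.
- Country design effect: 1 + (155/5 − 1) × 0.01 = 1.30, giving 201.5. A factor of 1.31 gives 203.05. The stated 203 is close.
- Attrition: 250 × 0.8 = 200 analysed. (203 / 0.8 = 254, against the stated 250.)

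With 1:1 allocation, 200 analysed means about 100 MT families in each phase.

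**2. Size of the planned test under therapist clustering**

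Assumptions, not in the documents: k therapists per phase, m = 100/k analysed MT families each, and therapist ICC ρ. Therapist effects in the two phases are taken to add.

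- Variance inflation of the difference: F = [1 + 1 + (m − 1)ρ] / 2
- Actual two-sided size: 2 × [1 − Φ(2.2414 / √F)]

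| k | m | ρ = 0.01 | ρ = 0.02 | ρ = 0.05 |
|---|---|---|---|---|
| 5 | 20 | F 1.095, 3.2% | F 1.190, 4.0% | F 1.475, 6.5% |
| 10 | 10 | F 1.045, 2.8% | F 1.090, 3.2% | F 1.225, 4.3% |
| 15 | 6.7 | F 1.028, 2.7% | F 1.057, 2.9% | F 1.142, 3.6% |
| 20 | 5 | F 1.020, 2.65% | F 1.040, 2.8% | F 1.100, 3.3% |

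Simulation agrees at k = 5. For ρ = 0.01 and 0.05 the t-test gives 3.2% and 6.5%, and the mixed model's contrast of baseline with 6 months gives 3.4% and 6.8%. With ρ = 0 the size is about 2.5%.

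**3. One therapist in both phases, with influence that acts once**

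By 6 months, half of the NICU standard-care arm has been randomized to post-discharge MT. Suppose each of 5 therapists serves one country in both phases, and a family carries the therapist's effect once whether treated in one phase or both. The NICU contrast then contains only half of each therapist effect. With total variance 1 and ρ = 0.05:

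- Variance of the difference: 0.25 × 0.05/5 + 0.95/100 + (0.5 × 0.95 + 0.5 × 1)/100 = 0.02175
- Ratio to the independent case: 0.02175 / 0.02 = 1.0875
- Size: 2 × [1 − Φ(2.2414 / √1.0875)] = 3.2%, and 3.2% by simulation

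The post-discharge contrast is symmetric.

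**4. Power, 100 analysed per arm**

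- No clustering: 4 / (8 × √(2/100)) = 3.536; Φ(3.536 − 2.2414) = 90%.
- Planned, uncorrected test with k = 5, ρ = 0.05: Φ[(3.536 − 2.2414)/√1.475] = 86%, at a true size of 6.5%.
- Corrected test with Satterthwaite degrees of freedom: about 60% for k = 5, ρ = 0.05. The arm variances are 0.64 × 1.95 = 1.248 and 0.64, with about 9 degrees of freedom. Power is about 79% for k = 5, ρ = 0.01, and about 78% for k = 10, ρ = 0.05.

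**The case against.** The case for leaving the plan alone has five parts.

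- **The premise is not documented.** No therapist count or ICC is given, and there is no inflation if the ICC is zero. Section 2.2.1 has fidelity rated from video, but that is quality control, not a statement that outcomes differ by therapist. This stands, and the point is therefore conditional.
- **Larger figures do not hold.** A reader might infer a size near 8% from 25 families per therapist. But 25 per country is the number allocated to MT before attrition. With 200 analysed over five countries the average is 20, which caps the size at 6.5% for an ICC of 0.05. Ten or more therapists bring it to 4.3% or less.
- **The factorial structure may cancel part of the effect.** This stands as a possibility (step 3). The documents do not say whether therapists are shared between phases or how their effects combine.
- **Power has slack.** If country largely cancels, the increase from 155 to 203 is a spare variance factor of 1.31. That matches a therapist ICC of 2 × 0.31/19 = 0.033 at 20 families per therapist, before small-sample degrees of freedom. This helps power but does nothing for size. A reader might also quote power of 75%, from Φ(3.536/√1.475 − 2.2414). That describes neither the planned test (86%) nor the corrected one (60%).
- **Generalizing beyond these therapists is partly a choice of estimand.** True, but section 2.3 makes the wider claim, and an interval that ignores therapist variation does not support it.

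**Conclusion.** The gap is real and its consequence is conditional. The planned test and models treat all MT families as independent, and nothing in the readable text handles therapist clustering. If outcomes differ by therapist, the standard errors for both MT effects will be too small.

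Under the assumed 5 to 20 therapists per phase, 100 analysed families per arm and an ICC of 0.01 to 0.05, the nominal 2.5% test runs at about 2.7% to 6.5%. The top of that range needs about one therapist per country and additive phase effects. With a shared therapist whose influence acts once, it is about 3.2%.

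A reader might conclude that the intervals are certainly too narrow, or that the primary analysis is invalid. The documents support neither, because they give no evidence on the therapist ICC or the caseload. This is a cheap improvement worth making, not a reason to replace the primary analysis.

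**What to change.** 1. State the number of therapists per site and phase, and record therapist identity for every MT participant in each phase.
2. Keep the primary analysis unchanged. Beside it, prespecify a partially nested sensitivity analysis: a therapist random effect that applies only to participants allocated to MT in that phase and is zero for standard care. With one therapist per site this becomes a site-by-arm random effect.
3. Let the therapist effect enter only measurements taken after that phase's MT has begun. Baseline precedes randomization, and a term that is constant over time would drop out of the change contrast.
4. Use small-sample degrees of freedom, such as Satterthwaite, and report the interval next to the primary one.
5. Qualify the generalizability statement in section 2.3 by that interval.

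The cost is one field on the session record and a paragraph in the SAP. The interval will be wider. With about five therapists the therapist variance is imprecisely estimated and power is clearly lower (about 60% at an ICC of 0.05). That is why this belongs beside the primary analysis and not in its place.
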